### Sample size

Sample size calculation was carried out, based on the changes in subjective craving after forced oral glucose intake as a primary outcome. Based on the pilot study [39], the lower confidence limit for the 95% confidence level (one-sided) was calculated as the base effect size of 0.38. Transferred to the scale for crossover design, this corresponds to an effect size of 0.76. Applied to an unpaired *t*-test with a significance level of 5% (two-sided) and a power of 90%, a *N*_0_ of 76 results. Assuming a dropout rate of 30% during the study, *N* = 108 patients should be included in the experiment. It is reasonable to assume that the number of cases calculated for the primary outcome is also sufficient for the fMRI data, as previous studies showed that effect sizes of brain activation changes are significantly higher than effect sizes of changes in behavioral studies [57].

### Statistical methods

#### Statistical analysis of anamnestic, psychometric, and hormone data

To analyze the anamnestic, psychometric, and hormone data, the statistic software IBM SPSS (Statistics – Advanced Statistics for Windows, version 26, IBM Corp., Armonk, NY) will be used. Descriptive data will be presented as statistical average (mean values) with standard deviations. To examine the difference in craving after exposition as a primary outcome, an unpaired *t*-test will be conducted. To determine the changes in craving and ghrelin and insulin plasma concentrations over the time during the measuring day and between the measuring days as the primary outcome, mixed linear models incorporating measurement repetition and crossover design will be calculated. Associations between changes in plasma concentrations of ghrelin and insulin and craving will be computed using the Pearson correlation coefficient.

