### Study objectives

The main aim of the present trial is to assess the potential effects of a forced oral glucose intake on changes of acute subjective craving within 70 (without fMRI measurement) to 100 min (including fMRI measurement) after the intake, which are modulated by changes in plasma concentration of acetylated ghrelin and insulin compared to a placebo intake (primary outcome).

Additionally, the study examines the effects of a forced oral glucose intake on mesolimbic cue reactivity in fMRI when confronted with alcohol-related cues, more precisely the neural brain activation (blood oxygenated level dependent (BOLD)) in the mesolimbic reward system during the presentation of alcohol cues and neutral cues compared to a placebo intake (secondary outcome).

Based on the presented state of research to date, the following hypotheses are proposed:A forced oral glucose intake leads to a reduction of subjective alcohol craving which is modulated by a reduction of acetylated ghrelin plasma concentration and simultaneously an increase of insulin plasma concentration.A forced oral glucose intake leads to a reduction of activation in the mesolimbic reward system after a confrontation with alcohol-related stimuli (cue reactivity) in fMRI, modulated by a reduction of acetylated ghrelin plasma concentration and simultaneously an increase of insulin plasma concentration.There is a positive association between the reduction of subjective alcohol craving, the reduction of cue reactivity in mesolimbic reward system, and the reduction of acetylated ghrelin plasma concentration such as the increase of insulin plasma concentration.

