### Randomization and blinding

According to the crossover design, all subjects go through both investigation conditions, the glucose and the placebo condition. Participants are allocated randomly to treatment order (glucose-placebo/placebo-glucose) with equal probability (1:1 ratio) by an independent pharmacy employee at the pharmacy of University Medical Center Heidelberg, using the RITA version 1.31 software (Randomization In Treatment Arms, Evidat, Germany) and a block randomization scheme with block sizes of 6. All participants will receive a unique anonymous identifying number used for the study documentation to ensure anonymity.

The study is conducted under double-blind conditions, so that neither the study staff nor the participants are aware of the assignment. Only the study manager, who is not directly involved in data collection, knows the order of conditions. The blinding will be maintained until all 108 subjects have completed the study and the database is locked. In the case of a medical emergency that requires knowledge of the treatment condition, the study staff can open the sealed envelope to unblind the study condition.

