**Fig. 2 Fig2:**
[figure not shown]
SPIRIT figure of the G-CuP study protocol

Changes in craving within 70 (no fMRI measurement) and 100 min (including fMRI measurement) after the glucose intake, as a primary outcome, will be measured by the Alcohol Urge Questionnaire (AUQ) at the beginning of each measuring day and visual analog scales (VAS) at eight time points during the trial. The AUQ consists of eight statements about the participants’ feelings and thoughts about alcohol consumption. The VAS includes the question “How high is your perceived craving for alcohol at this moment?” answered on an 11-item Likert scale ranging from “0 = no craving” to “10 = highest craving.”

fMRI measurements are conducted to examine the mesolimbic cue reactivity as a secondary outcome. The measurements are first conducted at a 3-T MAGNETOM Trio whole-body tomograph (Siemens, Erlangen, Germany) and after an upgrade in December 2021 at a 3-T MAGNETOM Prisma whole-body tomograph (Siemens, Erlangen, Germany) at the CIMH. Besides fieldmap and localizer, a functional resting state scan with eyes closed and a T1-weighted anatomical MPRAGE scan, the scan sessions contain the validated paradigms ALCUE [46] and NiCUEtin [47].

The nicotine-related mesolimbic stimulus reactivity is examined because of the high comorbidity between AUD and nicotine consumption and possible additive rewarding effects by combined consumption [48]. Besides, participants are asked to rate their current alcohol or nicotine craving on a visual analog scale during the paradigms.

Additionally, various self-assessment questionnaires (see Table 1) are assessed to detect possible covariates influencing the relationship of acetylated ghrelin and insulin plasma concentrations, subjective craving, and mesolimbic cue reactivity.

**Table 1 Tab1:** Questionnaires and psychometric scales incorporated in the study

Measure	Description
Alcohol Dependence Scale (ADS; [49])	Severity of the participant’s dependence on alcohol
Alcohol Urge Questionnaire (AUQ; [50])	Subjective alcohol craving
Obsessive Compulsive Drinking Scale (OCDS; [51])	Obsessive thoughts about alcohol use and compulsive behaviors related to drinking
Fagerström Test for Nicotine Dependence (FTND; [52])	Intensity of physical addiction to nicotine
Questionnaire of Smoking Urges (QSU; [53])	Subjective nicotine craving
Beck Depression Inventory (BDI II; [54])	Depressive symptoms
Perceived Stress Scale (PSS; [55])	Subjective stress

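### Neither primary craving analysis states an adjustment for same-day pre-drink craving, although craving is recorded at the start of each measuring day, so precision is given up at almost no cost

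*Protocol article*

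**What the plan says.** The objective concerns the "effects of a forced oral glucose intake on changes of acute subjective craving" (Study objectives), and the sample size is "based on the changes in subjective craving after forced oral glucose intake as a primary outcome" (Sample size). Craving is measured by the AUQ "at the beginning of each measuring day and visual analog scales (VAS) at eight time points during the trial" (Data collection and outcome measures).

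The section on anamnestic, psychometric and hormone data gives two analyses for the primary outcome. The first is an unpaired t-test of craving after exposure. The second covers changes in craving and hormones over the measuring day and between days, for which "mixed linear models incorporating measurement repetition and crossover design will be calculated". The article lists no fixed effects, covariates or covariance structure for this model.

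The data collection section also says that the Table 1 questionnaires, which include the AUQ, are collected to look for covariates of the relationship between hormones, craving and cue reactivity.

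**The concern.** In a two-day crossover, stable differences between participants already cancel out of the drink contrast. What remains is day-to-day variation within a person. A pre-drink craving value from the same day can remove some of it, but how much depends on how the value is used.

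- Ignoring it, as the t-test of post-exposure craving does, leaves that variation in the error.
- Subtracting it, as a change score does, also adds the baseline's own day-to-day noise. This helps only if the two day-to-day differences are strongly correlated.
- Fitting it as a covariate lets the data set the weight. Apart from one degree of freedom, this is never less precise than the other two.

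The protocol names the first option and, on the ordinary reading of the mixed model, the second. It does not state the third. At stake is the width of the interval for the primary drink effect.

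**Working it through.** **Inputs from the protocol.** The test is planned "with a significance level of 5% (two-sided) and a power of 90"%. For the effect, "the lower confidence limit for the 95% confidence level (one-sided) was calculated as the base effect size of 0.38", and "Transferred to the scale for crossover design, this corresponds to an effect size of 0.76". Sequences are allocated 1:1. Evaluable N is 76, and 108 are to be enrolled after 30% dropout.

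**Assumed.** r is the correlation between the day-to-day difference in pre-drink craving and the day-to-day difference in post-drink craving. The protocol does not give it, so a range is shown. Pre- and post-drink differences are taken to have equal SDs, with one post-drink value per day. All three options below are compared within person; whether the named t-test respects the pairing is a separate matter.

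**Step 1: the plan's own figure.** A two-sample t-test with effect 0.76 and 38 per sequence has noncentrality 0.76 × √(38/2) = 3.31 on 74 df, and power 0.905. So 76 is reproduced. Dropout: 76/0.7 = 108.6, against 108 stated.

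**Step 2: relative standard errors.** With the variance of the unadjusted post-drink difference set to 1, the change score has variance 2(1 − r) and the covariate-adjusted contrast 1 − r². The ratio of these two is (1 − r²)/(2(1 − r)) = (1 + r)/2.

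| r | Covariate vs change score, √((1+r)/2) | Covariate vs post-drink only, √(1−r²) | Change score vs post-drink only, √(2(1−r)) |
|---|---|---|---|
| 0 | 0.707 | 1.000 | 1.414 (41% wider) |
| 0.3 | 0.806 (19% narrower) | 0.954 (5% narrower) | 1.183 (18% wider) |
| 0.5 | 0.866 (13% narrower) | 0.866 (13% narrower) | 1.000 |
| 0.7 | 0.922 (8% narrower) | 0.714 (29% narrower) | 0.775 (23% narrower) |

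**Step 3: is the mixed model really a change score?** Exact generalised least squares was applied with one pre- and one post-drink value per day, complete data, period-by-time terms, 38 per sequence and within-person day SD 1. Three levels of between-person variance were tried. The post-only standard error is √(2/76) = 0.162.

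| r | Drink-by-time contrast | Pre-drink mean constrained equal across drinks | Post-drink only |
|---|---|---|---|
| 0.3 | 0.192 | 0.155 | 0.162 |
| 0.5 | 0.162 | 0.140 | 0.162 |
| 0.7 | 0.126 | 0.116 | 0.162 |

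The unconstrained contrast matches the change score. The constrained one matches covariate adjustment: the ratio of the two is √((1+r)/2) at every between-person variance tried.

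**Step 4: power at 76 evaluable.** The Sample size section bases its calculation on changes, so 0.76 is read as the change-score effect. Adjustment then turns it into 0.76/√((1+r)/2), on 73 df.

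| r | Change score | Post-drink only | Covariate-adjusted | Evaluable N for 90%, adjusted |
|---|---|---|---|---|
| 0 | 0.905 | 0.996 | 0.996 | 40 |
| 0.3 | 0.905 | 0.972 | 0.982 | 50 |
| 0.5 | 0.905 | 0.905 | 0.965 | 58 |
| 0.7 | 0.905 | 0.717 | 0.944 | 64 |

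**The case against.** The strongest reply is that the mixed model's terms are simply not listed, and an article may leave them to a fuller plan. If the pre-drink mean is constrained equal across drinks, the model is already about as efficient as covariate adjustment. Table 1, which includes the AUQ, also shows that covariates were contemplated. A reader might infer that the plan never adjusts for baseline; for the mixed model the text does not support that, since it is silent. What survives is narrower: the t-test takes no covariate as named, the mixed model's default contrast is a change score, and the Table 1 sentence is exploratory and commits the primary contrast to nothing.

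A reader might also infer that the trial is underpowered. If 0.76 were the effect on post-drink craving, a change score at 76 evaluable would have power 0.789 at r = 0.3 and 0.638 at r = 0. But the Sample size section rests on changes in craving, and on that scale the plan reaches its 90%. The lower figures do not follow from the document.

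Two further cautions stand. First, r is unknown and may be small, because the crossover has already removed stable person differences; at r = 0.1 or below the gain over post-drink craving is negligible. Second, the text does not time the eight VAS ratings relative to the drink, so a pre-drink VAS is likely but not confirmed. The day-start AUQ is a different instrument and may precede the cue exposure, so it may predict post-drink VAS less well.

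**Conclusion.** The point holds as a gain in efficiency. It is not an error in the plan's figures and shows no bias. One stated primary analysis is unadjusted, and the other gives same-day pre-drink craving no stated role. Adjusting would narrow the interval by about 8% to 19% against a change score, and by 5% to 29% against post-drink craving alone, for r between 0.3 and 0.7. These figures rest on equal SDs, a single post-drink value per day and an assumed r.

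The recommendation itself does not depend on r, since adjustment is not materially worse than either alternative anywhere in the range. It would usually matter more under the plan's fallback to first-day data when dropout exceeds 50%, because person differences then no longer cancel.

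**What to change.** Before unblinding, state the primary craving model as follows:

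- The response is post-drink VAS, with drink, measuring day, sequence and time as fixed effects and participant as a random effect.
- The covariate is the same day's last pre-drink craving rating, or the day-start AUQ if there is no pre-drink VAS. Enter it as the participant's two-day mean plus the day's deviation from that mean, so that only within-person variation adjusts the drink contrast.
- The pre-drink rating is then left out of the responses. Equivalently, keep it as a response with its mean constrained equal across drinks and a covariance that lets pre- and post-drink values correlate within a day.
- Report the change score as a sensitivity analysis.

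The cost is a sentence or two of analysis text and one or two degrees of freedom, with no new data. The blind is kept until all participants have finished and the database is locked, so the change can be made without knowledge of the results.

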#### Statistical analysis of fMRI data

To analyze the fMRI data, SPM12 (Wellcome Centre for Human Neuroimaging, Institute of Neurology, University College London, UK) running under Matlab R2020a (MathWorks, Natick, USA) will be used. Pre-processing will include motion correction, normalization to the Montreal Neurological Institute (MNI) template, and a spatial smoothing using an isotropic Gaussian kernel of 8 mm full width at half maximum (FWHM). Afterwards, first-level analyses (within-subject) modeling the experimental conditions (alcohol-related stimuli, neutral stimuli, rating phase via VAS) will be conducted for each participant in a general linear model. The resulting contrast images will be imputed into second-level analyses (between-subject) conducting induced brain activity regarding the effects of group and time using paired *t*-tests. To control for multiple statistical testing, the probability of a family-wise error (FWE) will be set to pFWE < 0.05. Associations between ghrelin and insulin plasma concentrations and cue-induced brain activation will be calculated using multiple regression analyses.

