Meanwhile, there is evidence that ghrelin also plays a role in the reward system, more precisely in the mesolimbic dopaminergic pathways and therefore in the development and maintenance of AD [13]. Dopaminergic neurons project from the ventral tegmental area (VTA) to the nucleus accumbens (NAc), the ventral striatum (VS), and afterwards into the prefrontal cortex (PFC) [14]. When dopamine release increases, people focus more on stimuli like food or alcohol and less on irrelevant environmental stimuli [15]. The acetylated form of ghrelin stimulates the activity of these dopaminergic neurons and therefore the activity of the mesolimbic reward system [16]. Consequently, higher concentrations of ghrelin go along with the higher activity of dopaminergic neurons and an increased focus on alcohol-related cues.

There is increasing evidence emphasizing the positive association of acetylated ghrelin and alcohol craving in early abstinence (for a review, see [17]). A preliminary study of our own working group including 41 AD patients during early abstinence confirms a positive association between acetylated ghrelin and subjective craving, with the effect mediated by cue-induced mesolimbic brain response [17]. A recent study [6] proves a significant increase in acetylated ghrelin plasma concentration in early abstinence, supporting the evidence of a further study of our working group, postulating that the acetylated ghrelin plasma concentration increases significantly during early abstinence [18]. The administration of ghrelin, for example, by intravenous injection, leads to significant higher cravings than the administration of a placebo [19]. The administration of a ghrelin receptor antagonist has the opposite effect: Preclinical animal intervention studies suggest that alcohol preference and consumption decrease after the administration of ghrelin receptor antagonists [20–25].

Preliminary studies could show positive associations between plasma concentration of acetylated ghrelin and brain activation in the striatum, as well as in the insula [17, 26]. Additionally, some studies postulate that intravenous administration of ghrelin leads to an increase in alcohol-associated brain activation in fMRI [27]. However, the systematic administration of a ghrelin receptor antagonist prevents ghrelin from increasing the release of dopamine in VTA and NAc and therefore reduces alcohol-related cue reactivity [25].

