## Methods

### Clinical trial design

The G-CuP (English: Glucose - Craving and Peptides) trial is designed as a monocenter randomized, double-blind, placebo-controlled, crossover trial examining two treatment arms. *N* = 108 individuals suffering from an AD and receiving a standard in-patient treatment (including withdrawal treatment, psychotherapeutic individual and group sessions, skills training, relaxation exercises, sports, occupational therapy, sociotherapy, pharmacotherapies if required, and aftercare planning) will be examined in the study.

Following the crossover design, participants will undergo both investigation conditions (glucose intake and placebo intake) on two measuring days within the first 7 to 21 days of abstinence. For each participant, the trial consists of a screening visit S0 (− 7 to − 1 day before T1) and two treatment visits T1 (day 0) and T2 (+ 3 to + 7 days). The crossover design was chosen because it is considered the gold standard for clinical trials. Fewer study participants are needed, even small effects of the intervention can be statistically proven and none of the participants is deprived of the intervention. The purpose of conducting a double-blind study is to prevent bias in the study results on the part of both the study investigators and the subjects.

The overall flowchart of the clinical trial design is shown in Fig. 1.

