### Trial status

Protocol version 1, 06/01/2022. The trial is ongoing, and participants are being actively recruited. Recruitment began in August 2020 and will be completed approximately January 2023.

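### The second-level fMRI comparison is fixed as paired t-tests, which give no period-adjusted treatment effect, although the craving and hormone models do allow for the crossover

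*Protocol article*

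**What the plan says.** Protocol article, Statistical analysis of fMRI data: contrast images from the first level go into second-level models "conducting induced brain activity regarding the effects of group and time using paired" t-tests, with family-wise error control. Time is not defined, and no period, sequence or scanner term is named. Hormone-activation associations are to be examined by multiple regression.

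Statistical analysis of anamnestic, psychometric, and hormone data: for craving and hormones, "mixed linear models incorporating measurement repetition and crossover design will be calculated".

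Clinical trial design and Randomization and blinding: each participant has "two treatment visits T1 (day 0) and T2 (+ 3 to + 7 days" later), and the order of conditions is allocated "with equal probability (1:1 ratio) by an independent pharmacy employee", in blocks of 6.

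Data collection and outcome measures: scanning began on a Trio system and continued "after an upgrade in December 2021 at a 3-T MAGNETOM Prisma whole-body tomograph". Trial status: "Recruitment began in August 2020 and will be completed approximately January 2023". The change of scanner therefore falls inside recruitment.

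Sample size: the figure derived for craving is carried over to fMRI. Risk assessment, risk management, and missing data: if dropout exceeds 50%, only first-day data are analysed.

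**The concern.** Each participant is scanned twice with the same cue paradigm, a few days apart, in early abstinence. A change between first and second scan is plausible from the document itself. The Background cites work of the same group "postulating that the acetylated ghrelin plasma concentration increases significantly during early abstinence", and links acetylated ghrelin positively to striatal and insular activation.

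A paired t-test makes one comparison. Paired by condition, it tests treatment and leaves any period difference in the data. Paired by visit, it tests period and says nothing about treatment. Running both still gives no treatment estimate adjusted for period.

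An unmodelled period difference moves the glucose-minus-placebo difference up in one sequence and down in the other. That enlarges the error term. If the two sequences have different numbers of completers, part of it also passes into the treatment estimate.

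**Working it through.** **1. The plan's own sample size.** Inputs from Sample size: an effect that "was calculated as the base effect size of 0.38", doubled to 0.76 on the crossover scale; unpaired t-test; two-sided 5%; power 90%; dropout 30%. With the noncentral t distribution, 38 per sequence gives power 0.905 and 37 gives 0.897, so N0 = 2 × 38 = 76, as stated. Then 76/0.70 = 108.6, against the stated 108. The doubling fits a comparison of first-minus-second differences between the two sequences (mean difference 2 × 0.38, SD 1), which is a period-adjusted crossover test. The number carried over to fMRI thus comes from a different test from the one named for fMRI.

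**2. Set-up.** Let D be a participant's glucose-minus-placebo difference, with SD 1 within a sequence. Its mean is d + π in one sequence and d − π in the other, where π is the period shift. Assumptions: d = 0.38, 76 completers, and the values of π and of the imbalance. The document gives no period effect for fMRI.

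**3. Equal completers (38/38).** The mean of D is unbiased with true standard error 1/√76. The paired test estimates a standard error too large by a factor of about √(1 + π²), which is 1.031 at π = 0.25 and 1.118 at π = 0.5. Approximate power is Φ(0.38√76 − 1.992 × factor), where 0.38√76 = 3.313:

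- π = 0: Φ(1.321) = 0.91
- π = 0.25: Φ(1.260) = 0.90
- π = 0.5: Φ(1.086) = 0.86

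Simulation gives 0.905, 0.893 and 0.857. For larger shifts it gives 0.79 at π = 0.75. With no true effect, the paired test rejects in about 3% of runs at π = 0.5 and 1.5% at π = 0.76, so it is conservative. The period-adjusted test has power of about 0.90 throughout.

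**4. Unequal completers.** Bias of the paired estimate = π(n1 − n2)/N.

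- 42/34, π = 0.5: 0.5 × 8/76 = 0.053. The estimate becomes 0.33 or 0.43, depending on which sequence loses more people; power is 0.73 or 0.94.
- 46/30, π = 0.38 or 0.76: bias 0.08 or 0.16; type I error 0.084 or 0.139.

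The adjusted estimate, the mean of the two sequence means, stays at 0.38. Its standard error at 42/34 is ½√(1/42 + 1/34) = 0.1153, against 1/√76 = 0.1147.

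**5. How likely is imbalance?** With 54/54 randomised and 76 completers lost without regard to sequence, a split of 42/34 or worse in either direction has probability 14% (hypergeometric), about 7% in a given direction.

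**6. Scanner.** A constant scanner shift cancels in D when both scans are on one machine, which a gap of 3 to 7 days makes true for nearly everyone. If two participants straddled the upgrade with a 1 SD shift (assumed), the estimate would move by at most 2/76 = 0.026 SD. If one scanner scaled activation by 1.5 in half the sample (assumed), type I error would be 0.048 and power 0.892 against 0.905.

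**The case against.** The plan says t-tests in the plural and names time, so separate tests of condition and of visit are a fair reading, and it is too much to say that period is disregarded. That stands as far as it goes, but separate tests still do not adjust the treatment effect.

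Shifts of 0.5 SD and above exceed the 0.38 SD effect itself, and nothing in the document supports a particular size. At 0.25 SD or less, with equal sequences, the loss is about 0.01 of power. The plan also expects larger effects in imaging than in behaviour: at 0.5 SD with a 0.5 SD shift, balanced power is still 0.98. The figures describe one test at 5%, not a family-wise corrected image analysis. All of this stands and limits the size of the point.

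A reader might infer that the fMRI result is bound to be biased or prone to false positives. The document does not support that: allocation is 1:1 in blocks, and with equal completers the paired test is unbiased and conservative. Bias needs unequal completers and can go either way.

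A reader might also infer that the scanner change undermines the secondary outcome. It does not, because scanner is constant within nearly every participant. With even accrual, about 16 of 29 months (55%) precede the upgrade, but that split matters only for comparisons across participants. Even in the first-day-only fallback, blocked allocation keeps scanner near balance between arms, so it adds noise rather than confounding.

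Finally, an analysis plan that is not shown may list covariates. That is a fair answer on scanner. It is weaker on period, because the article commits to a named test.

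**Conclusion.** The point holds in a limited form. The stated second-level test gives no period-adjusted treatment effect, while the same article builds the crossover into its craving and hormone models and takes its sample size from a test that adjusts for period. With equal completers the harm is lost power only: about 0.90 to 0.86 at an assumed 0.5 SD shift, and negligible at 0.25 SD or less. With unequal completers there is bias of π(n1 − n2)/N in either direction, about 0.05 SD at 42/34 with a 0.5 SD shift. These sizes rest on an assumed effect of 0.38 SD, 76 completers, and assumed shifts and imbalances. The planned 30% dropout makes some imbalance possible, though a large one is unlikely unless dropout depends on sequence.

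The scanner change does not materially affect the treatment contrast. It matters for hormone-activation regressions if these are run across participants, for the first-day-only fallback, and for the few who may have been scanned on both systems.

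**What to change.** - Replace the paired t-test with a second-level model containing participant, treatment and period. Equivalently, form each participant's first-minus-second-scan difference image and compare it between the two sequences.
- Define what time means in the fMRI analysis.
- Add scanner (Trio or Prisma) as a covariate in hormone-activation regressions run across participants and in any first-day-only analysis. It is not needed to remove a constant shift from the within-participant contrast.
- Run a sensitivity analysis without participants scanned on both systems.

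The cost is a change of specification in SPM12, made before unblinding. No new data are needed. The treatment contrast loses about one degree of freedom (75 to 74), and each covariate model loses one more for scanner.
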